**Data Management**

Data cleaning and storage:

Quantitative data will be entered using scan-ready forms and an optical scanner. Data will be entered and edited in Kenya. Images of scan forms will be kept on a secure server with access limited to study personnel. Data analysis will be undertaken collaboratively in Kenya and at CDC in Atlanta. Access to study computers will be restricted to study personnel, and paper records will be secured in locked cabinets in Kenya. Paper records will not be transported to Atlanta. Electronic files will be transferred to Atlanta either as password-protected e-mail attachments or as password protected files on zip disks or CDs.

Sample storage

Specimens will be stored in locked freezers or cabinets with identifiers at KEMRI and at CDC, to which only study personnel will have access.

In accordance with WHO advice, testing for serological responses to EPI antigens will be performed at a single commercial reference laboratory. The commercial laboratory will only have coded specimens, and will not be engaged in the research. Any remaining sera will be shipped back to Kenya.

Statistical analysis:

SAS software (SAS Institute, Cary, NC), and STATA software (STATA corporation, College Station, TX) will be used for quantitative data analysis. The primary analysis will be based on intention to treat. The analysis will be time to first clinical malaria comparing each of the study drug arms to the placebo arm. Mild, moderate, and severe anemia will also be compared between each study drug arm and the placebo arm.

**Time Frame**

Preparatory time

Preparatory time of approximately one month will be required to train facility-based study staff in clinical procedures and questionnaire administration, and to train field-based staff in patient tracking, cross-sectional surveillance, and the administration of household-based follow-up questionnaires.

Data collection

We estimate that there will be on average 139 visits/month at the 4 clinics at which enrollment will take place (Lwak, On’gielo, Abidha, and Saradidi or another comparable clinic in Asembo or Gem), based on 2001 utilization rates ([name], personal communication). If 80% of women offered accept enrollment into the study, then it should take approximately 14 months to enroll 1516 infants into the study. Since follow up will be for 2 years after the last child is enrolled, we estimate that data collection should take approximately 3.5 years. To allow for the possibility of slower than anticipated enrollment, we are budgeting 3 ½ years for complete data collection.

Preliminary data analysis and report preparation should require 6 months. Final manuscript preparation should require an additional 6 months.

Study results will be presented to local health authorities and to the participating communities at the conclusion of the study and analysis.

Good Clinical Practice

This conduct of this trial shall be guided by the principles of Good Clinical Practice (GCP).

##### Study Schedule

|  | 6  w | 10 w | 14 w | 18 w | 6 m | 9 m | 12 m | 18 m | 24 m |
| --- | --- | --- | --- | --- | --- | --- | --- | --- | --- |
| Enrollment | X |  |  |  |  |  |  |  |  |
| Clinic visit | X | X | X | X |  | X | X | X | X |
| Sickle Cell screening |  |  |  |  |  |  | X |  |  |
| Blood draw for G6PD testing |  | X |  |  |  |  |  |  |  |
| Study drug given |  | X | X |  |  | X |  |  |  |
| Blood film |  |  |  |  |  |  | X | X | X |
| Hemoglobin |  |  |  |  |  |  | X | X | X |
| Anthropomorphic measurements |  | X |  |  |  |  | X | X | X |
| Vaccinations | X | X | X |  |  | X |  |  |  |
| Blood for EPI antibody testing) | X |  |  | X |  | X | X |  |  |
| NP swab Hib |  |  |  |  |  | X |  |  |  |
| Iron Compliance |  |  |  |  | X |  |  |  |  |
| Filter paper |  | X |  |  |  |  | X |  |  |

#### Ethical Considerations

Informed consent procedures

All mother’s/guardians of children who are eligible for the study will be informed about the reason for the study. Each activity and requirement of the study will be explained to them. Informed consent forms will be translated into the local language (luo), and backtranslated to check for accuracy. Informed parental permission forms will be signed or thumb-printed (for women who cannot sign their names) for documentation of willingness to participate. If the woman is illiterate, a witness (not connected with the research study) will sign the permission form, attesting to the fact that the permission was accurately read or interpreted, and that participation and thumb-printing were given willingly without coercion. All women who are approached will be informed that their children’s entry into the study is voluntary and that they may withdraw from the study at any time.

Confidentiality

In order to protect the privacy of patients, only study personnel will have access to paper records, and those records will be kept in a locked file in Kisian. Computer records will be password protected, and only authorized study personnel will have access to those files.

## Risk/benefit information

Benefits to participating infants include free health care for routine childhood illnesses (malaria, anemia, diarrhea, and acute upper and lower respiratory infections) for a period of 24 months starting from the first day of that child’s enrollment in the study. The IPTi study ID card will also serve as a “health passport” which allows the child to receive free treatment for these conditions in one of the study health facilities for this period. The child will be seen by a dedicated study clinician, which may result in shorter wait times for medical care. Inpatient hospital costs at Lwak and Abidha hospitals will also be covered for enrolled children. Any other medical costs (e.g. specialty care) are not covered by the project unless the illness is deemed to have been caused by one of the study medications. All children will receive free iron, which has demonstrated benefits in reducing anemia. Not all children will receive routine antimalarials (i.e. the IPTi intervention) because the benefit of IPTi is not known in this setting. Because enrolled children will visit the clinic 5 extra times during the study, they are likely to have malaria and severe anemia detected and treated more quickly than usual. In addition, enrolled children will be receiving RDT and blood film diagnosis for febrile illnesses, which may allow for more accurate diagnosis and appropriate treatment of these illnesses. Guardians will be informed if an enrolled child has sickle cell disease deficiency, which might help to prevent adverse outcomes.

During weekends and evenings, a nurse will be available to assist IPTi participants who are severely ill. The nurse will be stationed at Lwak hospital, our most central study clinic. In cases where the infant must be hospitalized, the nurse will provide stabilizing treatment and the IPTi Field Supervisor, Coordinator, or designee will arrange transport to Bondo or Provincial hospital. This may benefit very ill infants. Guardians of infants who are critically anemic (Hb < 5) will be provided transport to a hospital (Kisumu or Siaya) for evaluation and treatment.

So that no costs are incurred by participating in this study, parents or guardians will be given a standard reimbursement for transport costs from their homes to the clinic and back when they bring their children for scheduled study visits. Parents or guardians will also be reimbursed for travel when it is necessary to bring the child to one of the study clinics after vomiting a dose of the study medication administered at home by one of the study compliance monitors. Standard reimbursement will be the average cost of a 'Boda-Boda' bicycle ride to and from the clinic, which is between 50 and 100 Kenyan Shillings, depending on distance

There a small risk from study medicines. Some children do not like the taste of iron. Some children complain of nausea and do not feel like eating. In some children the teeth will become darker. In other children the stool will become darker or greener than normal. This is a normal reaction to treatment with iron. The teeth and stool color will become normal again after the iron treatment is completed.

When given weekly as prophylaxis, SP has been associated with extremely rare severe cutaneous reactions such as toxic epidermal necrolysis and Stevens-Johnson syndrome [51].

Amodiaquine has rarely been associated with hepatitis and agranulocytosis in adults receiving the drug as weekly chemoprophylaxis [29-32], but a recent systematic review of studies of AQ for the treatment of malaria found no increase in adverse events when compared with CQ or SP, and found that all adverse events were minor or moderate, and not life threatening [34]. In children given AQ as a treatment dose, the drug appears safe [35, 36, 39], although an incidental finding of a decrease in neutrophil counts has been reported, without any associated clinical significance [35].

There are no reports of severe adverse reactions among children in trials using Lapdap for treatment of *P. falciparum* malaria [23, 25]. Occasional reports have been received of adult travelers developing agranulocytosis following Maloprim (a combination of dapsone and pyrimethamine) chemoprophylaxis, although usually after twice-weekly dosing, which is no longer recommended [52]. However, a study of chemoprophylaxis of Tanzanian infants with dapsone in combination with pyrimethamine (Deltaprim) found no evidence of toxicity [22].If any severe adverse reaction occurs among any enrolled child, the study code will be broken, the medication stopped, the reaction treated, and a note about drug allergy made on the child’s health card. Future episodes of malaria will therefore need to be treated with a different drug. Such reactions will be reported to CDC and KEMRI and to the institutional review boards of both institutions.

A small bruise or mild pain on the finger or the heel from where the blood (maximum 1.5 cc) is taken may develop. There is also a small chance of infection when blood is drawn. There is a small chance of temporary bleeding from the nasal swab.

Alternatives: Parents or guardians may choose not to have their child in the study. Children whose parent or guardian elect not to have their child enrolled in the study will be seen by the regular staff in the clinic. He/she will get the standard MOH care and pay any standard fees. No further visits would be required for these children.

**Adverse Event Reporting.**

Adverse Events: Any unexpected medical occurrence in a participant during the trial will be recorded as an adverse event. There are certain events detailed below which are anticipated to have a baseline rate, and are therefore not unexpected. These events will be reported in a summary statement as part of the yearly continuation. If the study team recognizes an increase above an expected rate, the information will be provided earlier than this annual report.

Because the postneonatal infant mortality rate in the IPTi study area is approximately 120 per 1000 infants, it is anticipated that approximately 170 children will die during the course of the study between enrollment (at 6 weeks of age) and the end of the primary study outcome period (at 12 months of age). Therefore, infant deaths from common causes (including malaria, diarrhea, pneumonia, malnutrition, bacterial sepsis, meningitis, other common childhood infections, injuries, prematurity, and congenital conditions) will be considered anticipated adverse events. Hospitalizations from such illnesses will also be considered expected adverse events. Deaths or hospitalizations from unexpected or unusual causes (examples: allergic reactions, non-viral hepatitis, Stevens-Johnson syndrome, toxic epidermal necrolysis, sudden unexplained death) or that in the judgment of the local PI are possibly or probably related to study drug administration will NOT be consideredexpected adverse events, and will be reported to the CDC as outlined below.

Adverse events that are serious, unexpected, and at least possibly related to study drug:

Adverse events that are serious (that is, results in death, is life-threatening (at the time of the event), requires inpatient hospitalization or prolongation of existing hospitalization, or results in persistent or significant disability), unexpected (meaning previously unobserved or undocumented in humans under the research intervention or one substantially similar), and at least possibly related to study drug administration (meaning the cause of the event is explained at least as well by the research procedures as any other cause) requires prompt reporting to the CDC and KEMRI IRBs. In such cases, initial informal notification of such an event shall occur by e-mail within 2 days of one of the principal investigators becoming aware of the event. Formal reporting (using CDc form 1254 and 1254s (where required) will occur within 2 weeks of the PI becoming aware of the event.

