# Executive Summary

# Approximately three quarters of preschool children in eastern Africa suffer from anemia, defined as a hemoglobin (Hb) concentration below 11 g/dL [1]. For children < 5 years of age, the overall incidence of severe malarial anemia (Hb < 5 g/dl) is estimated at 15-60 cases per 1,000 children per year [2]. Other studies have confirmed that the burden of malaria-related anemia falls primarily on infants and young children [3, 4]. Recently, Schellenberg and colleagues, working in an area of Tanzania with a low to moderate level of *Plasmodium falciparum* transmission and a low level of sulfadoxine-pyrimethamine (SP) resistance, demonstrated that by linking intermittent prophylaxis to routine immunization visits through the national Expanded Program on Immunization (EPI), SP could be administered to children at 2,3, and 9 months of age, resulting in a 59% reduction in rates of clinical malaria and a 50% reduction in the rate of severe anemia (Hb<8 g/dl) compared to those receiving placebo[5]. We propose to conduct randomized double blind placebo-controlled trial to estimate the efficacy of Intermittent Preventive Treatment for Infants (IPTi) with SP + three doses of artesunate (AS) (SP/AS3) given in combination with iron supplementation from 2-6 months of age at routine EPI visits on the prevention of clinical malaria, moderate anemia, and severe anemia in the first 12 months of life in an area with intense malaria transmission and near universal ownership of insecticide treated nets (ITNs). The primary objective is to compare the efficacy of iron supplementation and IPTi with one of 3 antimalarial regimens (SP/AS3, chlorproguanil-dapsone (Lapdap), or AQ/AS3) given at routine EPI visits with iron supplementation alone (+ placebo) on the prevention of clinical malaria in the first year of life. Specific secondary objectives are: 1) Compare the efficacy of iron supplementation plus IPTi with one of 3 antimalarial regimens (SP/AS3, Lapdap [chlorproguanil-dapsone], or AQ/AS3) given at routine EPI visits with iron supplementation alone (+ placebo) on the prevention of moderate and severe anemia in the first year of life; 2) Assess the impact of IPTi with the aforementioned regimens on serologic responses to EPI vaccines (Polio, Diphtheria, Tetanus, Pertussus, Hepatitis B, *Hemophilus Influenzae* type B, and Measles; 3) Assess the impact of IPTi with the aforementioned regimens (particularly SP/AS3) on the nasal carriage rates of *Haemophilus influenza* type b; and 4) Compare the efficacy of iron supplementation and IPTi with one of 3 antimalarial regimens (SP/AS3, Lapdap [chlorproguanil-dapsone], or AQ/AS3) given at routine EPI visits with iron supplementation alone (+ placebo) on the prevention of all-cause hospitalization in the first year of life. This trial will generate important public health information on the efficacy of IPTi in preventing anemia and clinical malaria among infants in an area with intense malaria transmission and ongoing prevention efforts through the use of insecticide treated nets. This trial will contribute towards understanding IPTi’s mechanism of action (i.e. through intermittent clearance of parasites vs. a chemoprophylactic effect afforded through the use of an antimalarial with a long half-life). The information gained will be useful to determine the safety of IPTi, and to decide what sort of antimalarials are appropriate for IPTi, and ultimately will help to direct child survival and malaria control policy in African countries. If alternative drug regimes to SP prove effective, that information will be valuable to policymakers as levels of *P. falciparum* resistance to SP rise with increased usage in east Africa.

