## Study drugs

As this is an efficacy study, all doses of antimalarials (or placebo) will be supervised. All enrolled infants will receive Day 1 dose(s) of study drugs during the 10 and 14 week intervention visits and again at the 9 month intervention visit. On days 2 and 3, parents will either be asked to return to the clinic for study drug administration, or the dose will be administered in the home by a compliance monitor. In the case of infants whose guardians were asked to return to clinic to receive the 2nd and 3rd doses of medication and who do not appear by noon of the appointed day, a compliance monitor will visit the home to administer the dose of medication. All medications will be dispensed as crushed tablets, not as commercial suspensions, in order to ensure accurate dosing. Mixing with syrup will be done at the moment of delivery to make the medicines more palatable.

*Sulfadoxine-pyrimethamine (SP) and artesunate*

SP (DAFRA Pharma, Belgium) will be given by the study team as crushed tablets suspended in syrup. The dose-equivalent will be one ½-strength tablet (250 mg sulfadoxine, 12.5 mg pyrimethamine) for all infants given a single time on the first day of treatment. The artesunate dose will be one 25 mg tablet, once daily for 3 days, also given as a crushed tablet in syrup.

*Chlorproguanil-dapsone (Lapdap)*

Lapdap (Glaxo-Smithkline, United Kingdom) will also be given as crushed tablets suspended in syrup. One pediatric LapDap caplet (15 mg chlorproguanil and 18.75 mg of dapsone) will be administered once daily for 3 days.

*Amodiaquine + artesunate* (DAFRA Pharma, Belgium)

Amodiaquine will be given as crushed tablets suspended in syrup. The dose will be one 67.5 mg tablet daily for 3 days. Artesunate will be given as for the SP arm.

*Placebos* (DAFRA Pharma, Belgium)

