## Intervention clinic visits

Enrolled infants returning to clinic at 10 weeks will be given study drugs and will be measured for recumbent length, weight, and mid-arm upper arm circumference. Capillary blood samples will be taken using finger or heel prick for later G6PD enzyme level testing. Blood will be collected on filter paper at the 10 week visit for later testing for genetic markers for drug resistance. Infants returning to the clinic at14 weeks will be given the 2nd dose of the study drugs. At the 9-month visit, infants will be given the final dose of the study drugs and a capillary blood sample will be taken for later measles serology testing.

A questionnaire soliciting information about overall health of the baby, febrile episodes, other intercurrent illnesses, use of other medications, ITN usage, and compliance with iron will be administered at each clinic visit. The form will be based on the OPD surveillance form used in the DSS, but will solicit more detailed information. Infants whose caretakers state that their child has been given CTX in the past 2 weeks will either a.) not be given the dose of intervention drug until 2 weeks after CTX was given, or b.) be withdrawn from the study (if CTX is given as a daily dose).

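### The protocol makes being unexpected a condition for recording an adverse event, so mild, known drug effects that do not lead to admission have no recording rule

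*Protocol*

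**What the plan says.** The recording rule is the opening sentence of Adverse Event Reporting: "Any unexpected medical occurrence in a participant during the trial will be recorded as an adverse event". The section then sets apart events with a known baseline rate: "These events will be reported in a summary statement as part of the yearly continuation". Those it lists are infant deaths from common causes and admissions for the same illnesses: "Hospitalizations from such illnesses will also be considered expected adverse events". Deaths or admissions from other causes are not treated as expected, and the illustrations are "examples: allergic reactions, non-viral hepatitis, Stevens-Johnson syndrome, toxic epidermal necrolysis, sudden unexplained death".

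For prompt reporting to the ethics boards, the same section gives the term a definition: "unexpected (meaning previously unobserved or undocumented in humans under the research intervention or one substantially similar").

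On what the safety data are for, the Executive Summary says: "The information gained will be useful to determine the safety of IPTi, and to decide what sort of antimalarials are appropriate for IPTi". The Justification repeats the safety use for policymakers. On contact with the infants, Study drugs says: "As this is an efficacy study, all doses of antimalarials (or placebo) will be supervised". Intervention clinic visits provides for "A questionnaire soliciting information about overall health of the baby, febrile episodes, other intercurrent illnesses, use of other medications, ITN usage" and iron compliance, on a form that is to go into more detail than the routine outpatient one.

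**The concern.** Whether an event was expected can be judged only once it has been written down. If that judgement decides what is written down, commonplace and already documented drug effects are the ones most likely to be lost, and different staff will lose different ones.

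These are preventive courses given at routine vaccination visits, so common mild effects bear on whether a regimen is suitable. Randomization against placebo is what separates a drug effect from background illness, and it helps only if events are collected by the same rule in every arm. No statistical analysis plan can recover events that the protocol did not require anyone to collect.

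**Working it through.** The point rests on the text; the plan gives no adverse-event figure to reproduce.

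**1. Follow one event through the rules.** Take an infant who vomits a supervised dose and is not admitted. Risk/benefit information foresees this, because it reimburses travel when a dose given at home is vomited and the child has to come to the clinic.

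| Rule (Protocol section) | What it covers | Is this event clearly recorded as an adverse event? |
| --- | --- | --- |
| Recording rule (Adverse Event Reporting) | Unexpected occurrences | Not clearly: vomiting a dose is foreseen |
| Yearly summary (same section) | Common-cause deaths and admissions | No: neither |
| Prompt ethics-board reporting (same section) | Serious, unexpected and at least possibly related | No: not serious |
| Reaction rules (Unscheduled visits; Risk/benefit information) | Severe reactions | No: mild |
| Reports to the DSMB | Adverse events: deaths, and hospitalizations and/or events possibly related to drug | Unclear: it starts from adverse events, and the wording leaves open whether admission is required |
| Travel reimbursement (Risk/benefit information) | Transport cost after a vomited home dose | No: nothing says the event is logged |

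**2. Compare the two uses of the key word.** Adverse Event Reporting names Stevens-Johnson syndrome and toxic epidermal necrolysis among unexpected or unusual causes. Risk/benefit information reports both as extremely rare reactions already associated with weekly SP prophylaxis. Under the later definition (previously unobserved or undocumented under the intervention or one substantially similar), an already documented reaction would not be unexpected. The same reaction is thus unexpected by the examples and arguably expected by the definition.

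**3. Check the timing of the other routes.** From the Study Schedule, courses start at 10 weeks, 14 weeks and 9 months. The next clinic visits are at 14 weeks, 18 weeks and 12 months, so the questionnaire follows about 4 weeks after the first two courses and about 3 months after the third. Outpatient forms depend on the family seeking care, and the Demographic Surveillance System section expects about 80% of children or their mothers to be linked to their records.

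**4. Count the contacts that already exist.** 1,516 infants x 3 courses x 3 days = 13,644 supervised contacts, an upper bound that assumes every infant completes every course.

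**5. What such data could show (illustration only; the event rates are assumed).** For two proportions with n per arm and p̄ = (p1 + p2)/2:

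power = Φ{ [ |p1 − p2| − z·√(2p̄(1 − p̄)/n) ] / √[ (p1(1 − p1) + p2(1 − p2))/n ] }

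For 5% against 10%, n = 379 and two-sided 0.05: p̄ = 0.075, the two standard errors are 0.01913 and 0.01905, and (0.05 − 1.96 x 0.01913)/0.01905 = 0.66, so power = 0.74. The Sample Size section's allowances of 10% loss and 13% mortality leave 379 x (1 − 0.23) = 292 per arm.

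| Placebo vs drug (assumed) | n = 379, alpha 0.05 | n = 379, alpha 0.017 | n = 292, alpha 0.05 | n = 292, alpha 0.017 |
| --- | --- | --- | --- | --- |
| 3% vs 8% | 0.86 | 0.74 | 0.76 | 0.60 |
| 5% vs 10% | 0.74 | 0.59 | 0.63 | 0.46 |
| 10% vs 18% | 0.89 | 0.79 | 0.80 | 0.66 |

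**The case against.** The best defence is that the sentence is loosely worded rather than restrictive. The section itself calls common-cause deaths and admissions adverse events, so an expected event can be one. On a natural reading, *unexpected* merely separates events handled individually from baseline-rate events summarized yearly, and a vomited dose or mild rash is not among those set aside. That reading is possible, but the text does not say it, and the definition a few lines later points the other way.

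Much of the rest of the defence stands, and it limits the point:

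- A reader might infer that only unexpected events are ever captured. They are not: expected deaths and admissions are reported too.
- A reader might infer that rash and jaundice are lost. The section treats allergic reactions and non-viral hepatitis as unexpected causes, though only of death or admission, and severe reactions have their own rules. Vomiting is the sound example.
- A reader might infer that mild effects go wholly unrecorded, or stay hidden from the DSMB. The questionnaire covers general health and intercurrent illness, parents are told to bring infants to study facilities for every illness, outpatient visits are put on a standard form, and one reading of the DSMB rule reaches possibly drug-related events without admission. The forms are not shown, so it cannot be said that they lack an item on reactions.
- A reader might infer that the trial cannot compare the tolerability of its three regimens. Tolerability is not a listed objective, and the planned comparisons are of each drug with placebo.

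The power figures depend on assumed rates, and at alpha 0.017 with 292 per arm they fall to between 0.46 and 0.66. They show that the contrasts are not hopeless, and are no evidence of the defect.

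**Conclusion.** The point holds in a limited form. The recording rule is badly fixed: it depends on expectedness, its stated exceptions cover only deaths and admissions, and its key word carries two meanings. Mild, known effects without admission therefore have no clear rule for recording as adverse events, and other routes capture them only in part. The result is weaker drug-versus-placebo safety information than the Executive Summary and Justification promise. The documents do not support saying that such events are entirely lost or that no tolerability comparison is possible.

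The size cannot be given as a number of missed events, because the protocol states no rates for mild reactions. The conclusion assumes that staff follow the written rule and that forms not shown do not already impose a wider one. It is a worthwhile, inexpensive repair and leaves the primary analysis untouched.

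**What to change.** In Adverse Event Reporting, replace *unexpected* with *untoward* in the recording sentence, and state that every untoward medical occurrence is recorded whether or not it is expected. Collect these events in all arms at the supervised day 1 to 3 contacts of each course and at the next scheduled visit, on a short common checklist.

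Use expectedness, seriousness and relatedness only to decide how quickly an event is reported. Give *unexpected* one meaning across Adverse Event Reporting and the Data Safety and Monitoring Board section, and say there whether possibly drug-related events without admission are included. Tabulate recorded events by arm against placebo for the DSMB and the final report.

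The cost is a few sentences, one checklist and some additional form entry; no new visits are needed.
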